relationship in which the lowest group (underweight and abstainers) has increased risk compared to those in the moderate categories. Reverse causality by unmeasured health problems may explain this pattern in these groups. In a Swedish intergenerational study, offspring BMI was used as an instrumental variable for own BMI as BMI in the offspring is less likely to be affected by health problems. The authors found less adverse consequences of lower BMI compared to conventional observational studies. Alcohol consumption in family members can be used similarly as instrument for own consumption to avoid the problem of sick quitters potentially producing non-causal increased risk compared to moderate drinkers (RQ 3). In both cases offspring alcohol and BMI are recorded earlier in life whereas CVD in parents is recorded at a higher age. More generally, using family proxies for exposure might be valuable not only to reduce reversed causality, but also because their alcohol intake will be less strongly associated with the individuals' other risk factors that predisposes him/her for CVD, i.e smoking and diet, and give less biased estimates of effect than own alcohol exposure.

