### **Data sources**

The Cohort of Norway (CONOR) Data from 10 epidemiological studies (n=181,891) from 1994-2003 have been merged into a national database. All the surveys included self-reported health and selected diseases, various risk factors, socio-demographic factors, use of medications and physiological measures such as blood pressure, cholesterol, triglycerides, waist and hip circumference, height and weight.

The Norwegian Twin Registry (NTR) Panel II were born 1915-1960. Questionnaires on alcohol consumption were sent out in 1980 and 1990 and 14 500 responded to one of these. These questionnaires included detailed reports on health and risk factors.

Norwegian Family Based Life course Study Data from all 7,400 000 Norwegian citizens alive between 1960 to 2010 has been linked to family data and several health surveys and registers. Family linkage is available for more than 90 % of those born after 1940. This is linked to several other cardiovascular health surveys in addition to CONOR (in total 730,000) and the Conscript Registry.

Hospital discharges on cardiovascular diseases in Norway (FS-data): Data on all cardiovascular hospitalizations in Norway between 1994 and 2009 has been obtained through patient administrative systems at Norwegian hospitals. This includes coronary heart disease (both myocardial infarction and unstable angina), stroke and atrial fibrillation.

Social security registry (FD-trygd): Data on disability pension, sickness and social security benefits on all Norwegian citizens from 1992 onwards. Diagnosis will be ICD-10: F01-F99 (Mental, behavioral and neurodevelopmental disorders)

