### **Samples (sub-populations)**

#### **RQ 1:**

The CONOR and the NTR will be pooled together and the NTR will be used as a cohort for this purpose. This will include n=47,848 from CONOR and n=8028 individuals from NTR (n=55,876 in total) with complete data on both moderate and binge drinking. Mean year of birth is 1947 in CONOR and 1941 in the NTR sample. More deaths occur in the NTR (n=1453 deaths) compared to CONOR (n=1805 deaths). Number of CVD deaths in the CONOR sample with follow-up until 2010 is 547. Based on the proportion of CVD mortality and all-cause mortality and number of fatal and non-fatal cases in the FS-database, total

number of cases, including both CONOR and the NTR is expected to be 3000 IHD and 3500 cases of stroke.

RQs 2 and 3:

This will include the CONOR and twin populations linked to the FS-data on hospital discharges, the Cause of Death Registry, the Conscript Registry (cognitive ability) and Social Security Registry (mental health problems). Two separate sub-populations of CONOR will be studied: all subjects who responded to items on moderate alcohol consumption (n=162,048) and, nested in this sample, those who responded to items on both moderate and binge drinking (n=47,848). In the first group there are 3774 deaths from CVD. There are in total 9735 acute myocardial infarction and 8926 stroke incident cases from the FS-database in CONOR. For the second group, see RQ1.

RQ 4:

This issue will be analyzed in a linkage between CONOR, cardiovascular health surveys in the Norwegian Family Based Life course study and the FS-data on hospital discharges. There are 116,037 individuals in CONOR with information on parents and siblings. Of these, 109,800 individuals have responded on the moderate alcohol consumption question with 9729 CVD deaths in fathers and 31,050 on the binge drinking question with 1854 CVD deaths occurring after the year of CONOR examination.

RQ 5:

CONOR: There are 48,401 siblings in CONOR with the same mother and father. 1025 of these have by 2010 died (281 CVD). We expect approximately 1400 CVD endpoints in the FS-database. For the second group on siblings, see RQ 1.

RQ 6:

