The Cause of Death Registry: All Norwegians alive in 1990 born after 1940 (n=1,095,000) will be followed up for death from with a main and underlying cause of death being alcohol-related dying in the period 1990-2012 (ICD-10: F10.0-F10.1, F10.3-F10.9, F10.2, K29.2 and K70). In a previous publication, we expect approximately 3500 alcohol-related cases. First degree family members will be followed up for CVD outcomes and mental distress CVD morbidity or mortality (The Cause of Death, FS-data and FD-trygd).

Questionnaire 1980 in NTR: In the NTR there are 5149 complete like-sexed twin pairs (n=10,298 individuals) who responded to the questionnaire on moderate alcohol consumption. 2021 individuals of these have died by 2010, including 810 CVD deaths. Based on the proportion CVD mortality and total mortality in the age group, number of fatal and non-fatal cases, and presuming they are followed up for hospital incidents from 1994, we expect approximately 1700 incident hospital cases of IHD and 1950 cases of cerebrovascular disease in the FS-database.

Questionnaire 1990 in NTR: And in the 1990 questionnaire there are 2138 complete twin pairs (n=4276 individuals) who have responded to the alcohol questionnaire in 1990 with information on both moderate and binge consumption. 626 of these individuals have died by 2010, 250 CVD deaths. Here we expect approximately 900 incident hospital cases of IHD and 1040 cases of cerebrovascular disease in the FS-database.

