**Main variables (see full description at [FHI webpage](#))**

**Moderate alcohol consumption**

Questions in CONOR:

1) “Approximately, how often have you during the last year consumed alcohol?” Eight response alternatives were recoded into five categories: Never/seldom, once per month, 2-3 per month, about once a week, 2-3 times a week, 4-7 times a week. 2) “When you drink, how many glasses do you usually drink?” 3) “When you drink, do you usually drink beer, wine or liquor?”

Questions in NTR:

1) “Do you drink beer?” 2) “Do you drink wine?” 3) “Do you drink liquor?” For each of these three questions, quantity was assessed by: “Do you drink less than a glass each day, 1-2 glasses each day or more than 2 glasses each day”.

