**Binge drinking**

Questions in CONOR:

“Approximately how often during the past 12 months have you consumed alcohol corresponding to at least 5 glasses of liquor in 24 hours?”

In all 47,848 participants (26,151 men and 21,697 women), and answers varied from zero to 99 times during the last year. Nearly half (46.3%) reported zero, and the frequency was a higher in men than in women.

In NTR:

1990 questionnaire: “Approximately how many times during one year do you drink more than 5 bottles of beer, one bottle of red or white wine or a quarter bottle of liquor?” (Never, 1-4 times a year, 5-10 times a year, once a month, 2-3 times a month, once a week, 2-4 times a week or every day or almost every day?)

Life course socioeconomic position: Highest educational level, household income (yearly updated), Childhood parental occupational class and education, and housing conditions from Censuses 1960 onwards).

Cognitive ability/Intelligence in late adolescence: The Norwegian National Conscript Service examines more than 90% of the male population at age 18-19 years. General ability is a composite score based on 3 speeded subtests. The Arithmetic Test (25 minutes) has 30 items in prose and measures logical reasoning and arithmetic and algebraic ability; it is similar to the arithmetic test in the Wechsler Adult Intelligence Scale (WAIS). The Word Similarities Test (8 minutes) is a multiple-choice test with 54 items, akin to the vocabulary test in WAIS. The Figures Test (20 minutes) has 36 multiple-choice items with 6 or 8 alternatives and is similar to Raven’s Progressive Matrices.

The CONOR mental health index: This consists of summative index including seven questions on mental distress scored 1-4: “Have you, in the course of the last two weeks, felt: Nervous and unsettled? Troubled by anxiety? Secure and calm? Irritable? Happy and optimistic? Sad/depressed? Lonely?” Response categories are “No”, “A little”, “Quite a bit” and “Very”. This index captures a combination of symptoms of anxiety and depression. This index has been validated, has good internal consistency and correlates highly with the total score for Hospital Anxiety and Depression Scale (HADS) ( $r=0.76$ ) and with Hopkins symptom checklist (HSCL-10) ( $r=0.70$ ).

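### NTR twins were asked about drinking in 1980 and 1990, but no link between the waves is described, so the 1990-based twin analyses cannot separate recent quitters from stable abstainers

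*Protocol*

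**What the plan says.** The Data sources section of the protocol describes two alcohol waves in one twin panel: "Questionnaires on alcohol consumption were sent out in 1980 and 1990 and 14 500 responded to one of these".

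The Samples (sub-populations) section treats them as two samples, each with its own expected case numbers. For 1980: "In the NTR there are 5149 complete like-sexed twin pairs (n=10,298 individuals) who responded to the questionnaire on moderate alcohol consumption". For 1990: "there are 2138 complete twin pairs (n=4276 individuals) who have responded to the alcohol questionnaire in 1990". RQ 1 adds to CONOR "n=8028 individuals from NTR (n=55,876 in total) with complete data on both moderate and binge drinking". These must be 1990 respondents, because the NTR binge item is shown for that wave only: "1990 questionnaire: “Approximately how many times during one year do you drink more than 5 bottles of beer".

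The NTR items shown under Moderate alcohol consumption ask about present drinking ("1) “Do you drink beer?” 2) “Do you drink wine?” 3) “Do you drink liquor"). No item on past drinking is shown. Nothing in the protocol describes linking the 1980 and 1990 answers of the same twin or using a change in drinking.

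The protocol does recognise the bias at issue. Its Approaches section proposes family members' consumption as an instrument "to avoid the problem of sick quitters potentially producing non-causal increased risk compared to moderate drinkers". Its Data analysis paragraph adjusts for self-reported CVD, diabetes, antihypertensive medication and psychosocial distress at baseline.

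**The concern.** One assessment of current drinking puts lifelong abstainers and people who have stopped in the same group. If some stopped because of illness, that group carries extra CVD risk, and moderate drinkers look protected by comparison. A second assessment of the same people ten years earlier identifies some of the quitters directly: drinking reported in 1980, none in 1990.

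The planned safeguards do not do this for the twins:

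- The instrument analysis (RQ 4 in the list of research questions) is set in CONOR, the other cardiovascular surveys and the hospital data. NTR is not named there.
- Adjustment for self-reported disease cannot deal with illness that was not reported, and the Approaches section attributes the pattern to unmeasured health problems.
- The co-twin comparison of RQ 5 removes what twins share. An illness that makes one twin stop drinking is not shared.

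At stake is the credibility of a protective estimate in the NTR part of RQ 1 and in the co-twin comparison that uses 1990 data.

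**Working it through.** **1. The stated counts are consistent.** 2 × 5,149 = 10,298 (1980 pairs). 2 × 2,138 = 4,276 (1990 pairs). 47,848 + 8,028 = 55,876 (pooled RQ 1). All agree with the protocol.

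**2. How many twins answered both waves.** The protocol does not say. Inputs: at least 10,298 respondents in 1980 (complete like-sexed pairs only, so a minimum), at least 8,028 in 1990 (those with moderate and binge data), and 14,500 from Data sources. The result depends on what 14,500 counts.

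- *At least one wave.* Both ≥ n1980 + n1990 − 14,500 = 10,298 + 8,028 − 14,500 = **3,826**. If 14,500 is rounded to the nearest hundred, the minimum lies between 3,777 and 3,876. As a share of the RQ 1 twins, 3,826 / 8,028 = 47.7%.
- *Exactly one wave.* Both ≥ (10,298 + 8,028 − 14,500) / 2 = **1,913**, and 1,913 / 8,028 = 23.8%.
- *Sum of the two pair samples.* 10,298 + 4,276 = 14,574, about 0.5% above 14,500. If that is its origin, 14,500 is not a count of distinct respondents and gives **no lower bound**.

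**3. Which analyses a 1980-yes, 1990-no twin affects.**

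- *1990 exposure* (8,028 in RQ 1; 2,138 pairs): the twin falls among the non-drinkers. Linkage would identify this person.
- *1980 exposure* (5,149 pairs): the same twin is already a drinker. Only those who stopped before 1980 sit among the abstainers, and a later wave cannot reveal them.

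The 5,050 endpoints given for RQ 5 equal 1,400 (CONOR siblings) + 1,700 + 1,950 (IHD and cerebrovascular cases expected in the 1980 twin sample). So 3,650 / 5,050 = 72% come from the sample whose abstainer group would not change. The 1990 pairs have their own expected cases: 900 + 1,040 = 1,940.

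**4. Weight of the twins in RQ 1.** Participants: 8,028 / 55,876 = 14.4%. Deaths: 1,453 / (1,453 + 1,805) = 1,453 / 3,258 = 44.6%. The 3,826 twins are 3,826 / 55,876 = 6.8% of the pooled sample.

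**5. Size of the bias, as illustration only.** Let q be the share of quitters among 1990 abstainers and RR their CVD risk relative to stable abstainers. Neither is in the protocol. The abstainers' risk is inflated by 1 + q(RR − 1), and a true null for moderate drinking would appear as the reciprocal.

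- q = 0.2, RR = 1.5: inflation 1.10, apparent ratio 1 / 1.10 = 0.91.
- q = 0.4, RR = 2: inflation 1.40, apparent ratio 1 / 1.40 = 0.71.

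These are assumed inputs, before any adjustment for baseline disease, and describe NTR abstainers only.

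**6. Timing.** The hospital data start in 1994, after both waves, so both answers can be used to classify twins before hospital follow-up begins.

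**The case against.** The strongest reply is that the protocol lists sample sizes here, not exposure coding. It never says that each wave will be analysed alone, it defines no NTR abstainer category, and it refers to a web page for the full variable description. Categories and sensitivity analyses are often left to an analysis plan. This stands in part: single-wave use is an inference from separately listed samples and the absence of any link. But the choice of samples and of exposure wave is made in this protocol, and the suggestion rests on data that the protocol itself describes.

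Several stronger readings are tempting, and the document does not support them.

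- A reader might infer that recent quitters contaminate the abstainers in both twin samples. In the 1980 sample they are coded as drinkers.
- A reader might infer that the counts prove an overlap of about 3,800. That holds on only one reading of an ambiguous sentence.
- A reader might set the 0.91 to 0.71 illustration beside the 0.75 that the protocol assumes for average consumption and conclude that quitters could explain it. The inputs are assumed, the planned adjustment is ignored, only part of the twins could be reclassified, and CONOR, the bulk of RQ 1, has a different lowest category (never or seldom) and no repeat measure described.
- A reader might infer that the protocol overlooks sick quitters or ranks them as the main threat. It does neither: they are one of several concerns about abstainers, alongside social selection, mental distress, cognitive ability and family factors, and it plans partial remedies.

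**Conclusion.** The point holds as a missed use of data in hand, not as an error or contradiction. In the 1990-based NTR analyses, as described, twins who stopped drinking between 1980 and 1990 are not distinguishable from stable abstainers, and the family instrument is not planned in that registry.

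The number who could be reclassified comes from twins with both waves: at least 3,826, at least 1,913, or without a lower bound, according to what 14,500 means. The effect on the hazard ratio cannot be computed from the document, because neither the share of quitters nor their risk is given. The conclusion assumes that the NTR items shown are the ones to be used and that no linkage is specified elsewhere.

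**What to change.** - State how many twins answered the 1980 questionnaire, the 1990 questionnaire and both, and what the 14,500 counts.
- Link the waves by person. In the NTR part of RQ 1 and in the co-twin analysis of the 1990 pairs, classify twins with both answers as stable abstainers, former drinkers (1980 yes, 1990 no), stable drinkers or new drinkers.
- Report the moderate-drinking hazard ratio with former drinkers kept in, and taken out of, the abstainer group. Make the comparison in the same twins, so that only the classification differs.
- Start follow-up after the 1990 questionnaire for deaths as well as hospital events. Otherwise the classification conditions on having survived to answer in 1990.

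Cost: no new data collection, one linkage within a registry and a small added analysis. The estimate will be less precise, because it uses only twins with both waves. It finds only quitting between 1980 and 1990, changes nothing for the abstainers of the 1980-based co-twin sample or of CONOR, and supplements rather than replaces the instrument and the baseline-disease adjustment.

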## **2. Aspects relating to the research project**

### **Background and status of knowledge**

Alcohol has a negative effect on many health-related outcomes but for heart diseases the effects seem to be mixed. Alcohol use is negatively related to hypertensive disease, hemorrhagic stroke and atrial fibrillation. For ischemic heart disease (IHD) and ischemic stroke (cardiovascular diseases, CVD), the relationship is complex. Chronic heavy alcohol use has been associated with adverse cardiovascular outcomes. But light to moderate drinking seems to be related to reduced risk of ischemic diseases.

It is not well understood to what extent frequent episodes of heavy alcohol consumption may counteract the beneficial effect on heart disease and by which mechanisms episodes of heavy alcohol have a negative effect on heart disease. Even rare and occasional episodes of binge drinking seem to increase the risk in a recent study from the northernmost part of Norway. One would expect the protective effect to be more pronounced in individuals who do not binge drink, and not present in individuals who report substantial binge drinking. A recent meta-analysis on binge drinking including only 4718 IHD events gave some support for this notion. Our study will add to this by 6500 CVD cases.

Norwegian studies on adolescent and adult abstainers have shown higher risk of psychosocial factors and might suggest a J-shaped pattern. A general finding is that abstainers tend to have worse health and are poorer. One interpretation of this and similar findings is that since alcohol is such an important token in social interaction, abstainers are likely to differ as a social group and have a wide range of individual characteristics that could put them at increased risk of several health problems. Those who have moderate intake have in studies been shown to have higher cognitive ability compared to abstainers and that heavy drinkers have lower cognitive ability.

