**Outcome variables:**

Cause of death registry and CVD diagnoses from hospitals (1994-2009): circulatory (ICD-10: I00-I99), coronary heart disease (ICD-10: I20-I25), stroke (ICD-10: I60-I69). Cardiovascular Disease in Norway (CVDNOR) is a register that contains all hospital discharge diagnoses (obtained from Norwegian hospitals, FS-data) for cardiovascular disease and diabetes, and also relevant procedures, such as surgery and cardiac interventions. CVDNOR covers the whole Norwegian population 1994-2009.

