## **Statistical methods**

Sample size and power: The materials used to address RQ 1 is considerably higher powered than those used in previous research. Power calculations have been conducted using the `sampsi` command in STATA and the program `Quanto` for interaction terms. RQ 1: Two options have been used: Either to report the effect of moderate alcohol consumption adjusted for binge drinking or to test formally for interaction between average alcohol consumption and reported binge drinking. We have calculated the last because we consider this the most conservative approach. The relative risk of main effects has for average alcohol consumption reported to be 0.75 and for binge drinking 1.45. If we assume that 10 % in the cohort develop CVD in the follow up period, power of 80 % and set p-value at 5 % for two sided tests, we would need a sample of 7,960 individuals, which is well below our sample of 55,876 individuals. RQ 2 and 3: Prevalence of mental distress in CONOR is on average 10 %, and the effect of depression on CVD is assumed to be 1.6. If we want to detect a 50 % difference in effect of binge between depressed and not depressed subjects, we would need 26,740 individuals (in our sample  $n=47,848$ ), and for frequency of alcohol use 53,680 individuals (in our sample  $n=162,048$ ). RQ 4: As we do not know the strength of association between alcohol consumption and sibling and parental CVD morbidity and mortality, it is difficult to calculate sample size exactly for this sub study. For this reason, we have preliminary investigated this issue, and found that it appears to be higher risk of CVD in fathers and same sexed sibling among those who are abstainers compared to those who drink moderately. The hazard ratio of CVD death in fathers among those who abstain from alcohol compared to moderate drinkers was 0.93 (0.88-0.99). RQ 5: It is not straightforward to estimate power in within sibling analyses. With a total of 5050 CVD endpoints, and based on our experiences in an analysis with similar design and number of endpoints, we consider it likely that we will be able to detect differences large enough to be theoretically interesting. RQ 6: With 3500 alcohol related cases, we consider it highly likely that we will be able to detect meaningful degree of familial aggregation for mental distress and CVD morbidity and mortality.

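### Stroke (I60-I69) and all circulatory disease (I00-I99) as outcomes are wider than the protocol's own ischaemic definition of CVD, and the planning figures mix the two

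*Protocol*

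**What the plan says.** The Protocol's section Background and status of knowledge separates two groups of conditions. The first is described as "Alcohol use is negatively related to hypertensive disease, 4 hemorrhagic stroke 5 and atrial fibrillation" (the numerals are citation marks). The sentence before it speaks of alcohol's negative effects on health, so the natural reading is harm. The second group carries the CVD label: "For ischemic heart disease (IHD) and ischemic stroke (cardiovascular diseases, CVD), the relationship is complex". The protective effect is placed in that group: "But light to moderate drinking seems to be related to reduced risk of ischemic diseases".

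The section Outcome variables then fixes the endpoints as "circulatory (ICD-10: I00-I99), coronary heart disease (ICD-10: I20-I25), stroke (ICD-10: I60-I69"). Stroke is not limited to the ischaemic type there or anywhere else. Data sources describes the hospital register as broadly: "This includes coronary heart disease (both myocardial infarction and unstable angina), stroke and atrial fibrillation".

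The planning figures for RQ 1 follow the wider definition. Under Samples, the "number of cases, including both CONOR and the NTR is expected to be 3000 IHD and 3500 cases of stroke". The background section uses the sum as its comparison with a meta-analysis of 4718 IHD events: "Our study will add to this by 6500 CVD cases". Under Statistical methods, "The relative risk of main effects has for average alcohol consumption reported to be 0.75 and for binge drinking 1.45". The source cited for these ratios is a review whose title in the reference list is confined to ischaemic heart disease. They are combined with an assumed 10% of the cohort developing CVD.

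**The concern.** The overall aim is to assess a possible protective effect of moderate drinking. On the protocol's own premise, two of its three outcomes combine conditions where protection is expected with conditions where alcohol does harm. The estimate for such an outcome is a weighted average. A stroke or I00-I99 ratio close to 1 could mean no protection, or protection offset by harm, and the outcome as coded cannot tell these apart.

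The formal RQ 1 test across binge strata could also be affected, under a condition the protocol does not state. If binge drinking raises the harmed types proportionally more than the ischaemic ones, those types take a larger share of events in the binge strata. The averaged ratio for moderate drinking then moves toward 1 in those strata, even if the ischaemic ratio is the same in all of them.

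The novelty claim and the power statement also join an effect reported for one disease to a count and a risk for another.

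**Working it through.** **Inputs from the Protocol.** 3000 IHD and 3500 stroke cases; 55,876 people; 6500 CVD cases; 4718 IHD events in the meta-analysis; ratios 0.75 and 1.45; CVD risk 10%; 80% power; 5% two-sided; 7,960 people required.

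**Assumptions, because the documents give no figures.** Haemorrhagic share of stroke s = 10-20%. Ratio for haemorrhagic stroke h = 1.0-1.45. Half the cohort exposed, for the power check.

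**1. The case count.** 3000 + 3500 = 6500, an exact match. Undivided stroke is 3500/6500 = 53.8% of it. The like-for-like figure to set beside 4718 IHD events is 3000. That is 3000/4718 = 64% of the meta-analysis total, where the text's comparison implies 6500/4718 = 138%.

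**2. The event risk.** IHD: 3000/55,876 = 5.4%. IHD plus all stroke: 6500/55,876 = 11.6%, or somewhat less if some people have both. The assumed 10% is not an IHD risk, while the ratios used with it come from IHD.

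**3. Stroke, moderate drinking.** With s as the share of events in the reference group, the mixed ratio is approximately (1 - s) × 0.75 + s × h.

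| s | h = 1.0 | h = 1.2 | h = 1.45 |
|---|---|---|---|
| 10% | 0.775 | 0.795 | 0.820 |
| 20% | 0.800 | 0.840 | 0.890 |

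For IHD and all stroke pooled, the two extremes are (3000 × 0.75 + 3500 × 0.775)/6500 = 0.763 and (3000 × 0.75 + 3500 × 0.89)/6500 = 0.825.

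**4. I00-I99, moderate drinking.** The same formula with an assumed non-ischaemic share of 20-40% gives 0.80 (20%, h = 1.0) to 0.93 (40%, h = 1.2). At h = 1.45 it gives 0.89, 0.96 and 1.03 for shares of 20%, 30% and 40%.

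**5. Is main-effect power lost?** Events needed = 4 × (1.96 + 0.842)² / (ln ratio)². This gives 380 at 0.75, 484 at 0.775 and 2,312 at 0.89. The protocol expects 3500 strokes, and power at 0.89 with 3500 events is 93%. Across the assumed range, main-effect power for stroke is not the problem.

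**6. The RQ 1 figure of 7,960.** It belongs to an interaction test and cannot be reproduced, because neither the interaction size nor the exposure prevalences are stated. The nearest variant tried (interaction ratio 1.5, half exposed to each factor, 10% events) gives 7.849/(0.0625 × (ln 1.5)²)/0.10 = 7,639, about 4% lower. As a rough guide to the effect of the risk alone, 7,960 × 0.10 = 796 events. At the expected IHD risk, that takes 796 × 55,876/3000 ≈ 14,800 people. This exceeds the stated requirement but is still well below 55,876.

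**The case against.** The case on the other side has real force.

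- **The outcomes are not all mixed.** A reader might infer that every endpoint blends benefit and harm. I20-I25 is listed separately and is purely coronary, and expected cases are already divided between IHD and stroke. A null for I00-I99 can be read beside the coronary result, so it is not wholly uninterpretable. This stands.
- **Atrial fibrillation is not a named outcome.** The sentence in Data sources describes register content. Atrial fibrillation enters only through I00-I99. This stands, and the point therefore rests on Outcome variables set against the background section.
- **A net effect is a legitimate target.** The title speaks of risk and benefit, and the policy question concerns circulatory disease as a whole. This stands as a reason to keep I00-I99. It does not explain why stroke, part of which carries the CVD label, is left undivided.
- **Binge drinking is different.** Its assumed ratio of 1.45 is already harmful, so adding harmed conditions does not cancel effects of opposite sign. This stands, and the dilution argument is confined to moderate drinking.
- **The harm ratios are not the protocol's.** The background speaks of alcohol use in general and gives neither dose nor ratio for the harmed conditions. This stands, so the size is shown only as a range that includes h = 1.0.
- **Stroke subtyping could be left to an analysis plan.** This stands in part. The ICD range does not forbid subtype analysis, but the protocol has fixed the codes and counted cases on them in a way that departs from its own definition.

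**Conclusion.** The mismatch between the CVD definition and the stroke and circulatory outcome codes is real and follows from the protocol's own text. It affects I60-I69, I00-I99 and the pooled CVD count, but not I20-I25. For moderate drinking, an ischaemic ratio of 0.75 would appear as about 0.78-0.89 for stroke under the assumed shares and ratios. For I00-I99 the range is wider and could pass 1 at the far end. The true size cannot be taken from the documents.

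A reader might infer that the study is underpowered as a result. The figures do not support this: main-effect power for stroke stays at 93% or more over the assumed range, and the interaction calculation cannot be checked. The damage is to interpretation.

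The planning figures have the same fault with no assumption needed: 3000, not 6500, is the number comparable with 4718, and the 10% risk does not match ratios reported for IHD, whose expected risk is 5.4%.

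**What to change.** - In Outcome variables, split I60-I69 into ischaemic and haemorrhagic stroke, with a stated rule for strokes of unspecified type.
- Name I20-I25 and ischaemic stroke as the outcomes on which the protective hypothesis is tested.
- Report haemorrhagic stroke, atrial fibrillation and hypertensive disease as separate outcomes.
- Keep I00-I99, labelled as a net-effect outcome.
- Restate expected cases for each outcome, and compare 3000 IHD cases, not 6500 CVD cases, with the meta-analysis.
- Redo the RQ 1 power statement with an event risk that matches the IHD-based ratios, and state the interaction size and exposure prevalences used.

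Settle this before analysis, so that the choice among outcomes with different expected directions does not follow the results.

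The cost is wording and recoding. The protocol says the register holds all cardiovascular discharge diagnoses, so no new data should be needed. The downside is fewer cases per outcome and some strokes that cannot be classified.
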